#### Rationale for the sham control

3.4.3

This study uses periganglionic normal saline injection as the sham control. The rationale for this design is based on the following considerations:

##### Procedural matching and blinding maintenance

3.4.3.1

Normal saline injection is highly consistent with active SGB in terms of needle trajectory, ultrasound imaging, procedural tactile sensation, and postoperative subjective experience. This ensures effective blinding of participants and outcome assessors, minimizing assessment bias that could arise from procedural differences.

##### Absence of specific sympathetic blockade effect

3.4.3.2

Normal saline lacks the nerve conduction blocking effect of local anesthetics and therefore does not produce the specific sympathetic inhibitory effects of SGB (e.g., ipsilateral skin temperature increase, Horner’s syndrome). It has no specific therapeutic effect, consistent with the basic definition of a sham control.

##### Controllability of non-specific effects

3.4.3.3

Although the injection procedure may produce minor mechanical stimulation or placebo effects, such non-specific effects are balanced between the two groups and are substantially smaller than the specific SGB effects mediated by local anesthetics. Several previous randomized controlled trials of SGB have used normal saline injection as a sham control, confirming its effectiveness in maintaining blinding and controlling bias (13).

Therefore, the normal saline sham control design used in this study balances the two key principles of blinding maintenance and absence of specific intervention effects, representing a scientifically valid and literature-supported approach.

### Safety management

3.5

#### Operator qualifications

3.5.1

All SGB procedures in this study will be performed by anesthesiologists with at least 3 years of experience in ultrasound-guided nerve blocks. Each operator must complete a dedicated SGB training program and pass an institutional competency assessment, demonstrating the ability to identify vascular variations, adjust the needle trajectory, and manage potential complications independently.

#### Safety measures during the procedure

3.5.2

(1) Pre-procedural assessment: All patients will undergo routine coagulation testing (PT, APTT, INR, platelet count) before the procedure, and anticoagulation management will strictly follow established guidelines for discontinuation or bridging. Pre-procedural ultrasound examination will be performed to evaluate cervical vascular anatomy, identify the positions of the common carotid artery, vertebral artery, and internal jugular vein, and rule out contraindications such as anatomical variations, severe vascular tortuosity, or cervical masses.(2) Intra-procedural monitoring: Throughout the block procedure, patients will be continuously monitored with electrocardiography, non-invasive blood pressure, and pulse oximetry. An intravenous line will be maintained, and emergency medications (atropine, dopamine, lipid emulsion, etc.) will be readily available. A three-step aspiration-injection-aspiration technique will be employed: after needle placement, aspiration is performed to confirm no blood or cerebrospinal fluid; 1 mL of normal saline is injected to assess resistance; then local anesthetic is injected slowly in divided doses, with re-aspiration after each 1 mL injection to prevent intravascular or intrathecal injection.(3) Adverse event monitoring: An independent DSMB has been established for this study, consisting of experts in anesthesiology, neurology, and biostatistics. The DSMB will oversee the safety of the entire study, regularly review adverse event data, and have the authority to recommend study suspension or termination if safety concerns arise.

#### Post-block monitoring protocol

3.5.3

After the procedure, patients will be transferred to the post-anesthesia care unit (PACU) or ward and monitored for at least 2 h with continuous vital sign assessment. Key monitoring observations include: voice quality, swallowing function, respiratory rate, chest wall excursion (to rule out pneumothorax), neck swelling (to rule out hematoma), and upper limb sensory/motor function (to rule out brachial plexus involvement).

If hoarseness or dysphagia occurs, patients will be placed in a semi-recumbent position to prevent aspiration, and otolaryngology consultation will be arranged if necessary. Patients with no abnormalities after 2 h may be transferred to the general ward, where ward nurses will continue monitoring according to the nursing record sheet for up to 24 h post-procedure.

#### Anticoagulation management

3.5.4

The following perioperative anticoagulation management protocol will be followed: Aspirin (oral): Discontinue 7 days before the procedure. Clopidogrel: Discontinue 7 days before the procedure. Warfarin: Discontinue 3–5 days before the procedure; recheck INR before the procedure, target INR < 1.5. Low molecular weight heparin: Discontinue 24 h before the procedure.

For special cases, consultations with cardiology and vascular surgery will be arranged to develop individualized bridging protocols. The block will be performed only after confirming no contraindications to anticoagulation.

#### Emergency response for local anesthetic systemic toxicity (LAST)

3.5.5

If early symptoms of LAST (perioral numbness, tinnitus, agitation, tachycardia) occur, immediate actions include: stop injection, administer oxygen, and maintain airway patency.

If seizures or convulsions develop, administer propofol or midazolam intravenously to control seizures, and perform endotracheal intubation if necessary.

If circulatory depression occurs, administer intravenous epinephrine and fluid resuscitation to maintain blood pressure.

Administer 20% lipid emulsion according to standard protocol: initial bolus of 1.5 mL/kg, followed by continuous infusion at 0.25 mL/kg/min. Continuous monitoring of electrocardiography, blood pressure, and oxygen saturation is required, and intensive care unit consultation should be arranged if necessary.

#### Systematic adverse event reporting

3.5.6

Mild adverse events (e.g., transient hoarseness, mild dysphagia, local pain) will be recorded by the operating physician within 24 h using an adverse event reporting form and reported to the study coordinator.

Serious adverse events (e.g., LAST, severe hematoma, pneumothorax, nerve injury, death) will be reported to the ethics committee, DSMB, and institutional adverse event management department within 24 h of discovery.

All adverse events will be documented with details on time of occurrence, severity, management measures, and outcomes. Regular summary reports will be submitted to the DSMB for review.

Stopping rule: If two or more serious adverse events directly related to SGB occur, the DSMB may recommend early termination of the study.

### Standardized perioperative management

3.6

To ensure that any observed intergroup differences are primarily attributable to the study intervention (SGB or sham block), all participants receive a strictly standardized perioperative care protocol encompassing anesthesia, analgesia, and delirium prevention strategies.

#### Standardized anesthesia protocol

3.6.1

Anesthesia is managed according to a uniform protocol for induction, maintenance, and emergence.

(1) Preoperative management: Adherence to strict fasting guidelines (8 h for solids, 2 h for clear liquids). Premedication with benzodiazepines is avoided.(2) Induction: Following standard monitoring establishment, anesthesia is induced with intravenous sufentanil, ciprofol, and cisatracurium. The exact doses are determined as follows: Sufentanil: 0.3 μg/kg for ASA III or age ≥75 years; 0.5 μg/kg for ASA I-II and age <75 years. Propofol: 0.4 mg/kg for age ≥75 years or ASA III; 0.5 mg/kg for age <75 years and ASA I-II. Cisatracurium: 0.15 mg/kg for age ≥75 years or ASA III; 0.2 mg/kg for age <75 years and ASA I-II.(3) Maintenance: Anesthesia is maintained with sevoflurane (end-tidal concentration 1.0–1.3 MAC, age-adjusted) and a continuous remifentanil infusion. Remifentanil infusion rate is initiated at 0.10 μg/kg/min and adjusted within the range of 0.05–0.20 μg/kg/min to maintain heart rate and blood pressure within ±20% of baseline. Higher rates (0.15–0.20 μg/kg/min) are used for patients <70 years or those with a history of chronic opioid use; lower rates (0.05–0.10 μg/kg/min) are used for patients ≥75 years or those with baseline bradycardia. Supplemental boluses of sufentanil (5–10 μg) are administered if blood pressure or heart rate increases by >20% from baseline. Muscle relaxation is maintained with intermittent cisatracurium as needed. Ventilation is controlled to maintain end-tidal carbon dioxide between 35 and 45 mmHg.(4) Hemodynamic management: Mean arterial pressure (MAP) is maintained within ±20% of baseline. A decrease in MAP >20% is primarily treated with intravenous ephedrine (6 mg bolus). An increase in MAP >20% is managed by deepening anesthesia (increasing sevoflurane concentration or administering supplemental sufentanil).(5) Emergence: Approximately 30 min before the anticipated end of surgery, ketorolac tromethamine (30 mg IV) is administered, and the remifentanil infusion is discontinued. Extubation is performed upon meeting standard criteria (consciousness, adequate spontaneous respiration, SpO₂ > 95% on room air).

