#### Active intervention (SGB group)

3.4.1

Patients in this group will receive two stellate ganglion blocks: The first block will be performed on the afternoon before surgery. The second will be performed 30 min before the induction of general anesthesia on the day of surgery.

Lateralization: All blocks will be performed on the right side at the C6 level. The right side is selected for the following reasons: (1) right-sided SGB is associated with a lower risk of esophageal injury and has a more predictable anatomical relationship between the stellate ganglion and adjacent structures; (2) right-sided sympathetic blockade may have a more favorable effect on cardiac autonomic balance (reducing sympathetic outflow to the heart) compared to left-sided block; (3) previous pilot studies on SGB for perioperative neurocognitive outcomes predominantly used right-sided approach, facilitating comparison with existing literature.

Under sterile conditions and real-time ultrasound guidance (C6 level), a 22-gage needle will be advanced to the prevertebral fascia. After negative aspiration, 3–5 mL of 0.375% ropivacaine will be injected (Figure 2). Successful blockade will be confirmed by the development of Horner’s syndrome (ptosis, miosis, anhidrosis) and/or ipsilateral skin temperature increase ≥1.5 °C within 15 min.

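### The induction text in 3.6.1 names ciprofol but gives doses for propofol; secondarily, the 2 h post-block monitoring in 3.5.3 does not fit a second block given 30 min before induction

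*Protocol article*

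**What the plan says.** **Induction agent (protocol article, 3.6.1, item 2).** The regimen is set out in one sentence: "anesthesia is induced with intravenous sufentanil, ciprofol, and cisatracurium". The next sentence opens with "The exact doses are determined as follows" and gives doses by age and ASA class for three drugs. The entry for the hypnotic reads: "Propofol: 0.4 mg/kg for age ≥75 years or ASA III; 0.5 mg/kg for age <75 years and ASA I-II". The other two entries are for sufentanil and cisatracurium. Ciprofol has no entry.

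**Post-block monitoring (3.5.3 and 3.4.1).** For the period following a block, section 3.5.3 states: "patients will be transferred to the post-anesthesia care unit (PACU) or ward and monitored for at least 2 h with continuous vital sign assessment". The listed observations are voice, swallowing, respiratory rate, chest wall movement, neck swelling, and sensation and movement of the arm. The section does not separate the first block from the second. On timing, 3.4.1 states: "The second will be performed 30 min before the induction of general anesthesia on the day of surgery". Section 3.4.2 gives the sham procedure the same two time points.

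**The concern.** The first contradiction lies in an operative dosing instruction. Someone following 3.6.1 literally has a drug without a dose and a dose for a drug outside the stated regimen. Two anesthesiologists could read it differently and each claim to have followed the protocol. This matters for safety. It also weakens two things the design relies on: 3.6 argues that group differences can be attributed to the block because co-interventions are uniform, and 3.6.4 records any departure from the anesthesia protocol as a deviation. Neither works cleanly while the induction hypnotic is ambiguous.

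The second contradiction is one of timing. A patient who is anesthetized 30 min after the second block cannot also spend the following 2 h in the PACU or on the ward having speech, swallowing and arm function checked. Hoarseness and dysphagia are named safety outcomes in 3.7.3, so it should be clear how they are to be looked for after that block.

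**Working it through.** No sample size, power or alpha figure is involved. The check is a comparison of text and one subtraction.

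**Step 1. Drug names in 3.6.1, item 2.**

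| Drug | In the induction sentence | In the dose list |
|---|---|---|
| Sufentanil | yes | yes |
| Ciprofol | yes | no |
| Propofol | no | yes (0.4 or 0.5 mg/kg) |
| Cisatracurium | yes | yes |

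Two of the three drugs match and the hypnotic does not.

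**Step 2. Does another section settle it?** Ciprofol appears nowhere else in the article. Propofol appears once more, in 3.5.5, for control of seizures in local anesthetic toxicity, which has no bearing on induction. Maintenance in 3.6.1 uses sevoflurane and remifentanil. The article therefore does not show whether the drug name or the dose line is the slip.

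**Step 3. Reach.** Every participant is induced under this text: 87 per group × 2 = 174 (3.8).

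**Step 4. Monitoring window for the second block.**
- Required (3.5.3): at least 2 h = 120 min.
- Available before induction (3.4.1): 30 min.
- Remainder: 120 − 30 = 90 min, and 90 / 120 = 75% of the minimum period.
- Anticipated surgery lasts 2 to 6 h, because shorter or longer procedures are excluded (3.2.2, item 6). The remaining 90 min is shorter than the shortest anticipated operation (120 min), so the window normally closes before the patient wakes.

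**Step 5. What the remaining 90 min can still cover.** Under the anesthesia protocol the patient has neuromuscular blockade and controlled ventilation.
- Still observable: vital signs and neck swelling.
- Not assessable: voice, swallowing, and sensation and movement of the arm.
- Not possible as written: the move to the PACU or ward after the procedure.

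The first block, on the afternoon before surgery, has no such conflict.

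**The case against.** On the induction text, it can fairly be said that both arms share the same inconsistent instruction, so it favors neither, and that it may be no more than a one-word slip. Both points stand as far as they go. They mean that no effect on the treatment comparison is shown and that the clinical size of the risk cannot be judged from the article. They do not remove the contradiction. Nor does condensation for a journal explain it, since the article chose to print the doses and called them exact.

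On monitoring, the case against is stronger, and most of it stands:

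- Section 3.5.3 does not require the patient to be awake for 2 h. Its explicit continuous element is vital signs, which are followed in theater.
- The 30 min before induction is usable. Section 3.4.1 expects signs of a successful block within 15 min, so early voice or arm effects can be checked.
- Ascertainment goes on after the 2 h. Ward monitoring runs up to 24 h after the procedure (3.5.3), mild events are recorded within 24 h with their time of occurrence (3.5.6), and Table 1 schedules adverse event collection on day 0, daily on days 1 to 3 and at discharge.
- Sham participants have the same procedure at the same times and the same anesthetic, so hoarseness from airway management can arise in both arms.

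A reader might infer that adverse events after the second block will be under-counted or misattributed so as to distort the safety comparison. The documents do not support that. What is left is narrower: brief effects on voice, swallowing or the arm may pass unseen during anesthesia. In a single patient, hoarseness first noticed after extubation has two possible explanations.

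**Conclusion.** The contradiction in 3.6.1 holds as stated. The induction hypnotic that is named has no dose, and the one that is dosed is not named. It affects the operative text for all 174 planned participants and should be corrected before anyone is enrolled. A reader might go further and conclude that a wrong dose has been prescribed. The article does not show which sentence is in error, so the supportable conclusion is only that the two disagree and must be reconciled.

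The conflict between 3.5.3 and 3.4.1 also holds, as a secondary point limited to the second block. At least 90 of the 120 min fall under general anesthesia, and three of the listed observations cannot be made in that time. This assumes that the 2 h runs from completion of the block and that induction follows 30 min later as planned. It would be too strong to say that the 2 h of monitoring cannot be done at all, since part of it continues in theater, or that the group comparison of adverse events is biased.

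**What to change.** 1. **Section 3.6.1.** The sponsor's clinical team should make the named induction agent and the dosed agent agree, and carry the correction into every working document that uses this text. No drug or dose is proposed here.
2. **Sections 3.5.3 and 3.4.1.** The clinical team should reconcile the post-block monitoring text with the timing of the second block, so that it is clear what applies when induction follows 30 min later. No monitoring rule is proposed here.

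No extra field on the adverse event form is needed. Section 3.5.6 already records when each event occurred, and the two blocks fall on different days.

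The cost is a wording correction in each place, reported through the amendment route in 3.11. Section 3.1.1 states that no participant had been enrolled at submission; if that is still so, the correction can be made before the first induction.

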#### Standardized postoperative analgesia

3.6.2

After extubation, all patients are connected to a standardized patient-controlled intravenous analgesia (PCIA) pump. Crucially, this analgesia protocol is applied identically to both the SGB and sham groups. The PCIA solution contains hydromorphone (0.15–0.2 mg/kg), nalbuphine (1.0–1.5 mg/kg), and ondansetron (16 mg), diluted to 100 mL with normal saline. Doses are calculated based on ideal body weight: Hydromorphone: 0.15 mg/kg for age ≥75 years or eGFR <60 mL/min; 0.2 mg/kg for age <75 years and normal renal function. Nalbuphine: 1.0 mg/kg for age ≥75 years; 1.5 mg/kg for age <75 years. Ondansetron: 16 mg (fixed dose, independent of body weight). The pump is set to a basal infusion of 1.0 mL/h, a bolus dose of 2.0 mL, a lockout interval of 15 min, and a 1-h limit of 8.0 mL. Rescue analgesia (hydromorphone 0.2–0.4 mg IV) is provided by the acute pain service team if pain is inadequately controlled (NRS ≥ 4) by the PCIA. Total opioid consumption (in morphine milligram equivalents, MME) will be recorded for the first 48 h postoperatively and compared between groups as a secondary outcome.

#### Multicomponent delirium prevention bundle

3.6.3

All patients receive a non-pharmacologic, multicomponent delirium prevention strategy throughout their hospitalization, adapted from the ABCDEF bundle:

Assess, prevent, and manage pain.

Both spontaneous awakening and breathing trials (when applicable).

Choice of analgesia and sedation.

Delirium: assess, prevent, and manage.

Early mobility and exercise.

Family engagement and empowerment.

Specific interventions include regular reorientation, provision of sensory aids (glasses, hearing aids), encouragement of early mobilization (beginning on postoperative day 1), sleep hygiene promotion (minimizing nocturnal disturbances), and active involvement of family members in care.

To ensure protocol adherence, a daily compliance checklist is developed, recording the completion of each component (reorientation, sensory aids, early mobilization, sleep hygiene, family involvement). Adherence rates will be reported and compared between groups.

#### Control of confounding variables

3.6.4

To minimize the potential impact of confounding variables on the primary outcome (POD incidence), the following measures will be implemented:

(1) Standardized perioperative management: As described in sections 3.5.1–3.5.3, all patients (both groups) will receive identical anesthesia, analgesia, and delirium prevention protocols. Any deviation from these protocols will be recorded as a protocol deviation.(2) Data collection on potential confounders: The following predefined variables, known to influence POD risk, will be collected and adjusted for in the statistical analysis: age, sex, body mass index (BMI), ASA physical status, baseline MoCA score, duration of surgery, intraoperative blood loss, intraoperative use of vasopressors, and postoperative opioid consumption (MME).(3) Statistical adjustment: In addition to the primary intention-to-treat analysis, a multivariable logistic regression model will be used to adjust for the above confounders, reporting adjusted odds ratios (aOR) with 95% confidence intervals.(4) Sensitivity analysis: A sensitivity analysis excluding patients with major protocol deviations (e.g., those who did not receive the allocated block, or those with incomplete primary outcome data) will be performed to assess the robustness of the findings.

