#### Analysis of primary outcomes

3.9.2

The cumulative incidence of POD on postoperative days 1–3 will be compared between groups using the Chi-square test, and relative risk (RR) with a 95% confidence interval (CI) will be reported. A supplementary multivariable logistic regression will be performed to adjust for pre-specified covariates: age, baseline MoCA score, and ASA physical status. To obtain adjusted relative risk instead of odds ratio, modified Poisson regression with robust standard errors will be adopted for covariate-adjusted analysis. Multivariable logistic regression will be used only as a supplementary approach when convergence issues occur.

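### The supporting adjusted analysis of postoperative delirium conditions on four variables that arise after the blocks, and sections 3.6.4 and 3.9.2 specify it differently

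*Protocol article*

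**What the plan says.** Section 3.6.4 (Control of confounding variables) lists age, sex, BMI, ASA status, baseline MoCA and then "duration of surgery, intraoperative blood loss, intraoperative use of vasopressors, and postoperative opioid consumption (MME"). It describes all nine as "known to influence POD risk, will be collected and adjusted for in the statistical analysis". The model follows: "In addition to the primary intention-to-treat analysis, a multivariable logistic regression model will be used to adjust for the above confounders". The result is to be an adjusted odds ratio with a 95% confidence interval.

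Section 3.9.2 (Analysis of primary outcomes) makes the chi-square test with a relative risk the main comparison. It then plans a supplementary logistic regression to "adjust for pre-specified covariates: age, baseline MoCA score, and ASA physical status". The next sentences adopt modified Poisson regression with robust standard errors for the adjusted analysis, in order to report a relative risk, and add: "Multivariable logistic regression will be used only as a supplementary approach when convergence issues occur".

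Section 3.6.2 says of opioid consumption that it "will be recorded for the first 48 h postoperatively and compared between groups as a secondary outcome". Section 3.7.2 lists it among the secondary outcomes.

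**The concern.** A variable measured after treatment can carry part of the treatment effect, or can be changed by the outcome. Adjusting for it does not remove confounding in a randomised trial, and it changes what the treatment coefficient means. Section 3.6.4 presents this model as its control of confounding for the primary outcome, so readers will take it as the robustness check on the main result. A real effect could then look fragile, or a weak one could look stronger than it is.

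The second problem is independent of the first. The two sections describe different adjusted analyses, and each calls its covariates fixed in advance. Nothing in the article says which one is to be reported as the adjusted result.

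**Working it through.** **1. Timing of the covariates.** Section 3.4.1 places the blocks on the afternoon before surgery and 30 min before induction.

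| Variable in 3.6.4 | Before or after both blocks | Link to the block in the article |
|---|---|---|
| Age, sex, BMI, ASA, MoCA | Before | None possible |
| Duration of surgery | After | None stated |
| Blood loss | After | None stated |
| Vasopressor use | After | Plausible: 1.2 and 3.4.1 describe reduced sympathetic outflow |
| Postoperative opioids (MME) | After | Secondary outcome (3.6.2, 3.7.2) |

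MME is summed over the first 48 h, while POD is assessed on postoperative days 1 to 3. The windows overlap, so delirium may alter patient-controlled opioid use before the covariate is complete.

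**2. The two specifications side by side.**

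| | 3.6.4 | 3.9.2 |
|---|---|---|
| Covariates | 9 (5 baseline, 4 post-block) | 3 (age, MoCA, ASA) |
| Model | Logistic | Modified Poisson |
| Effect measure | Adjusted odds ratio | Adjusted relative risk |
| Role of logistic | The adjusted model | First planned outright, then only if convergence fails |

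**3. The plan's own sample size, and what rests on it.** Section 3.8 assumes 40% versus 20%, two-sided alpha 0.05 and 80% power. With unpooled variance, n per group = (1.960 + 0.842)² × (0.40×0.60 + 0.20×0.80) / 0.20² = 7.849 × 0.40 / 0.04 = 78.5, against the stated 78. Allowing for 10% dropout, 78 / 0.90 = 86.7, so 87 per group and 174 in total, as stated. This is built on the unadjusted chi-square test and does not depend on any adjusted model.

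**4. Events per parameter.** Expected events are 78 × (0.40 + 0.20) = 46.8 with 78 evaluable per group, and 87 × 0.60 = 52.2 with 87. Each covariate counts as one parameter, plus one for treatment.

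- 3.6.4, nine covariates: 46.8/10 to 52.2/10 = 4.7 to 5.2.
- The five baseline covariates of 3.6.4 only: 46.8/6 to 52.2/6 = 7.8 to 8.7.
- 3.9.2, three covariates: 46.8/4 to 52.2/4 = 11.7 to 13.1.

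**5. Illustration of the bias in the planned odds ratio.** The article gives no effect of the block on MME, so every input here is assumed. The marginal risks are held at 40% and 20%, so the unadjusted odds ratio is (0.20/0.80) / (0.40/0.60) = 0.375. One normally distributed covariate M is added, with logit P(POD) = a + t × treatment + b × M. The block shifts the mean of M, exp(b) is the odds ratio of POD per SD, and a and t are solved to give the two marginal risks. The adjusted odds ratio is exp(t).

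| Shift in M caused by the block | OR per SD 1.3 | 1.6 | 2.0 |
|---|---|---|---|
| −0.8 SD | 0.46 | 0.52 | 0.60 |
| −0.5 SD | 0.42 | 0.45 | 0.48 |
| −0.3 SD | 0.40 | 0.41 | 0.42 |
| None | 0.37 | 0.36 | 0.34 |
| +0.3 SD | 0.34 | 0.31 | 0.28 |

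If the block lowers M, the odds ratio moves towards 1. If it raises M, as could happen with vasopressor use, the odds ratio moves away from 1. With no shift, the small change is non-collapsibility of the odds ratio, not bias. Reverse causation from delirium to opioid use is not modelled.

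**The case against.** The strongest reply is that nothing confirmatory rests on this. The primary analysis is the unadjusted chi-square test with a relative risk, and 3.6.4 places its model in addition to that analysis. Sample size, alpha and the interim boundary do not depend on the adjusted model. This stands in full. A reader might infer that the effect under test is itself diluted, or that the primary result could be picked afterwards; the article does not support either. Only the supporting estimate is open.

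A reader might also infer that adjustment must pull the estimate towards no effect, or that all four variables are mediators. The article does not support that either. It gives no mechanism for duration or blood loss, and the case is strongest for MME and vasopressor use. The direction depends on how the block shifts each variable, and the table shows both directions. Nor does the mismatch between sections remove any effect; it only leaves the choice of model open.

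Finally, the illustration rests on assumed inputs, and an odds ratio near 0.60 needs the extreme corner of the range. That is conceded. None of these points is a reason to keep post-block variables in an adjustment list or to keep two rival specifications.

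**Conclusion.** The concern holds for the supporting covariate-adjusted analysis of the primary outcome and goes no further. Section 3.6.4 commits to adjusting for four variables that arise after both blocks. One is a declared secondary outcome whose window overlaps the delirium assessments, and another is plausibly changed by a sympathetic block. The resulting odds ratio need not estimate the total effect of the block. Bias is absent, apart from non-collapsibility, if the block does not change these variables and delirium does not affect them. The move from 0.375 to about 0.40 to 0.60 holds only for an assumed 0.3 to 0.8 SD fall in MME and an assumed odds ratio of 1.3 to 2.0 per SD.

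The conflict between 3.6.4 and 3.9.2 on covariates, model and effect measure needs no assumption; it is on the page. The nine-covariate model would also be thin, at about 5 expected events per parameter.

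**What to change.** - In 3.6.4, delete duration of surgery, blood loss, vasopressor use and postoperative MME from the adjustment list.
- In both 3.6.4 and 3.9.2, state the same single adjusted analysis: modified Poisson regression with robust standard errors, treatment plus one list of pre-randomisation covariates, reporting an adjusted relative risk. The 3.9.2 set (age, MoCA, ASA) serves. Sex and BMI are also baseline variables and may be added, provided they appear in both places.
- Remove the contradiction in 3.9.2 about logistic regression. Any fallback for non-convergence should also report a relative risk, so that the effect measure does not change with the model.
- Report the four post-block variables descriptively by group, or in a mediation analysis labelled exploratory.

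The cost is a wording amendment, notified to the ethics committee, registry and investigators as 3.11 requires for important modifications. No extra data or patients are needed. Section 3.1.1 says that nobody had been enrolled when the manuscript was submitted and that recruitment was planned from February 5, 2026. If enrolment has begun, the change should be dated and made before any unblinded outcome data are seen.
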